## Abstract

**Background:**

Patients with COVID-19 and hypoxaemia despite conventional low-flow oxygen therapy are often treated with high-flow nasal cannula (HFNC) in line with international guidelines. Oxygen delivery by helmet continuous positive airway pressure (CPAP) is a feasible option that enables a higher positive end-expiratory pressure (PEEP) and may theoretically reduce the need for intubation compared to HFNC but direct comparative evidence is lacking.

**Methods:**

We plan to perform an investigator-initiated, pragmatic, randomised trial at an intermediate-level COVID-19 cohort ward in Helsingborg Hospital, southern Sweden. We have estimated a required sample size of 120 patients randomised 1:1 to HFNC or Helmet CPAP to achieve 90% power to detect superiority at a 0.05 significance level regarding the primary outcome of ventilator free days (VFD) within 28 days using a Mann-Whitney *U* test. Patient recruitment is planned to being June 2020 and be completed in the first half of 2021.

**Discussion:**

We hypothesise that the use of Helmet CPAP will reduce the need for invasive mechanical ventilation compared to the use of HFNC without having a negative effect on survival. This could have important implications during the current COVID-19 epidemic.

**Trial registration:**

ClinicalTrials.gov NCT04395807. Registered on 20 May 2020

## Introduction

### Background and rationale {6a}

Patients requiring hospitalisation for COVID-19 predominantly present with acute hypoxaemic respiratory failure (AHRF) [1]. Conventional low-flow oxygen therapy will suffice for patients with mild to moderate disease but patients with severe or critical illness will require more advanced support [2]. Endotracheal intubation and mechanical ventilation constitute the highest level of care for patients with AHRF but beds and ventilators in the intensive care unit (ICU) are limited. High-flow oxygen therapy through a nasal cannula (HFNC) is a mainstay of treatment in patients with COVID-19 failing on conventional oxygen therapy in our institution and has recently been endorsed in the surviving sepsis campaign (SSC) guidelines on COVID-19 [3]. HFNC have been shown to improve comfort, oxygenation and 90-day survival, but not intubation rates, compared to standard low-flow oxygen therapy in patients with AHRF [4]. Non-invasive ventilation (NIV) using a continuous positive airway pressure (CPAP) should theoretically improve lung aeration and gas exchange in AHRF compared to HFNC because it enables a higher positive end expiratory pressure (PEEP), similar to that of mechanical ventilation [5]. Yet, NIV is receiving mixed support in relation to COVID-19 [3]. This originates from some observational studies that have reported high failure rates and associated high hospital mortality when using conventional CPAP face masks where tolerance is a well-known issue [6, 7]. In comparison to masks, Helmet CPAP show superior tolerance, significantly reduced intubation rates and improved survival in AHRF and acute respiratory distress syndrome (ARDS) respectively [8, 9]. A systematic review from 2017 found a significant reduction in hospital mortality from using Helmet CPAP in AHRF but stated that there was insufficient evidence to make clear recommendations [10]. The SSC guidelines on COVID-19 make a similar conclusion, positioning the Helmet CPAP as a feasible option for patients with COVID-19 failing on conventional oxygen therapy, but authors were unable to make specific recommendations due to a lack of direct evidence [3]. Helmet CPAP have been used extensively to treat COVID-19 in northern Italy with anecdotally good results [11]. It is our hypothesis that the use of Helmet CPAP will reduce the need for intubation in patients with AHRF from COVID-19 compared to the use of HFNC, without having a negative effect on survival.

## Objectives {7}

### Primary objective

To compare the performance of Helmet CPAP versus HFNC regarding the number of ventilator free days (VFD) within 28 days in patients with COVID-19 and AHRF.

Secondary objectives:
To evaluate oxygen delivery efficacy after 1 h on the Helmet CPAP versus HFNCTo compare the level of patient-reported comfort after using the Helmet CPAP versus HFNC at 24 h from randomisationTo investigate the relative incidence of carbon dioxide rebreathing in patients using Helmet CPAP versus HFNCTo compare the short-term (28 days) and longer-term (180 days) all-cause mortality in patients randomised to Helmet CPAP versus HFNCTo compare the frequency of intubation in patients randomised to Helmet CPAP versus HFNC

## Trial design {8}

Investigator-initiated, randomised, controlled, investigator-blinded, pragmatic superiority trial with a parallel group design, 1:1 concealed allocation ratio and a 28-day main follow-up period.

## Methods: participants, interventions and outcomes

### Study setting {9}

A medical emergency care ward functioning as an intermediate-level COVID-19-cohort in Helsingborg hospital, Region Skåne, Sweden. The hospital is a teaching emergency hospital that serves a population of approximately 250,000. Helsingborg Hospital is a suitable institution for this trial because the hospital has both the Helmet CPAP and HFNC in regular use and southern Sweden is still expecting its COVID-19 epidemic peak.

### Eligibility criteria {10}

Patients will be screened for eligibility by the attending ward physician (specialist in internal medicine) using the following criteria:

Inclusion criteria (all of the following):
Age ≥ 18 yearsSars-Cov-2 found in the respiratory tract by PCR during the current disease episodePeripheral oxygen saturation (SpO2) < 92% *despite* conventional low-flow oxygen therapy of at least 6 L/min for at least 15 minA decision to initiate HFNC or Helmet CPAP by the attending ward physicianThe patient has given written informed consent to participate

Exclusion criteria (any of the following):
Need for direct admission to the intensive care unit for mechanical ventilationUnconsciousness or drowsinessPneumothoraxCarbon dioxide pressure (pCO2) > 6 kPa in venous blood gas (VBG)Underlying chronic obstructive pulmonary disease stage III-IVA decision not to participateInability to comprehend the study content and give informed consent

### Who will take informed consent? {26a}

The attending ward physician (a specialist in internal medicine) will be responsible for obtaining informed consent from trial participants prior to randomisation. The physician will provide oral and written information about the study, any risks or benefits involved with participation and inform that termination from the study can be done at any time without explanation in accordance with the ethical approval. Patient information will be provided as early as possible when patients are admitted to the intermediate-level COVID-19 cohort ward and generally when they are still on low-flow oxygen therapy to allow adequate time to make an informed decision.

### Additional consent provisions for collection and use of participant data and biological specimens {26b}

The data collected for this study may be used in ancillary studies, but we have no plans to collect additional participant data or biological specimens outside of what is mentioned in this protocol.

## Interventions

### Explanation for the choice of comparators {6b}

HFNC is endorsed as the standard treatment for patients with COVID-19 failing on conventional low-flow oxygen therapy (i.e. the target study population) in both local treatment guidelines and current international guidelines [3].

### Intervention description {11a}

#### Intervention

Helmet CPAP (CaStar hood for CPAP therapy by Starmed/Intersurgical) driven by high-flow blender (Bio-Med Devices).

#### Control

HFNC (Optiflow™ nasal high-flow interface) driven by AIRVO 2 humidification system (Fisher and Paykel).

Interventions will be initiated at the time of randomisation and both the Helmet CPAP and HFNC will be applied and titrated according to local best standard of care (SOC). Hereby, HFNC will be started at a flow of 30 L/min with a possibility to increase flow to maximum 60 L/min at the choice of the attending physician (corresponding PEEP ~ 3–5 cmH_2_O [12]). Helmet CPAP will be started at a flow of 40 L/min and a PEEP of 5 cmH_2_O which can be increased to a maximum of 20 cmH_2_O at the attending physician’s discretion. We suspect that the PEEP will normally be used at around 8–10 (− 12) cmH_2_O. The study provides no guidelines on fraction of inspired oxygen (FiO2%) or litres of oxygen per minute. Oxygen settings will be titrated according to the attending physicians’ choice. Local SOC guidelines recommend a target SpO2 of 92%. When patients allocated to the intervention needs to take off the helmet for short periods of time (e.g. for meals), they will generally be put on HFNC according to physician’s choice. Included patients who require transportation from the medical COVID-cohort to the ICU for mechanical ventilation will be put on a portable HFNC during transportation between wards and prior to intubation according to the wishes of our local intensivists. Extubated patients will also be put on HFNC regardless of treatment allocation according to the wishes of our local intensivists. We believe that these circumstances will only have a moderate effect on the primary outcome because we expect the time from transportation to intubation to be short and we expect the number re-intubations within 28 days to be few.

### Criteria for discontinuing or modifying allocated interventions {11b}

There are no mandated criteria for discontinuing or modifying allocated interventions, but the patient and the treating physician may choose to do so at any time, upon which they will be asked to report timing and reason for non-adherence. Patients moving to the ICU due to deterioration or to a regular ward due to clinical improvement will be able to adhere to the standard protocol follow-up. In the (improbable) event of a patient being moved while having an unchanged need for respiratory support to another hospital or ward that does not have the treatment device available allocated to the patient (i.e. Helmet CPAP), we will regard this as an allocation violation, but we should still be able to assess the primary outcome on an “as randomised”-basis. Patients on the Helmet CPAP will necessarily have to take off the Helmet for shorter periods of time during meals. We will actively register the number of hours spent in each device each day on a case report form (CRF) as a continuous evaluation of allocation adherence. More than 6 h per 24 h off the allocated device will be registered as an allocation deviation.

### Strategies to improve adherence to interventions {11c}

The Helmet CPAP can be associated with discomfort from bad fit and airflow noise. Patients will be provided with earplugs and we will carefully select strap system and helmet size (XS, S, M, L or XL) to ensure optimal fit for each patient. High airflow levels in HFNC can be a discomfort which is why we recommend a starting flow of 30 L/ min and allow titrations at the choice of the treating physician in consultation with the patient.

### Relevant concomitant care permitted or prohibited during the trial {11d}

We make no restrictions on concomitant care or interventions during the trial.

### Provisions for post-trial care {30}

We have no plan for ancillary or post-trial care or compensation for the participants. This is a pragmatic trial comparing two current standards of care.

### Outcomes {12}

#### Primary outcome

Ventilator-free days (VFD) within 28 days after randomisation. Patients who die within 28 days will be counted as 0 VFD. Time in ventilator will be counted in hours and rounded to whole days (continuous data).

Secondary outcomes:
SpO2/FiO2 ratio assessed 1 h after randomisationPatient comfort 1–10 (visual analogue scale) assessed 24 h after randomisationFrequency of endotracheal intubation within 28 days from randomisationFrequency of carbon dioxide rebreathing (pCO2 > 6 kPa in a VBG) within 28 days from randomisationDays alive within 28 days from randomisationDays alive within 180 days after randomisation (not in primary publication)

#### Outcomes rational

Based on the best current evidence [4, 9], we expect any difference in efficacy between intervention and control to be due to a difference in intubation rate and/or possibly time in respirator rather than survival. Respirator use is a particularly clinically relevant outcome during the current COVID-19 pandemic when ICU beds are scarce. The benefit of choosing VFD as a primary outcome rather than intubation frequency is that VFD strongly penalises death. Hereby, VFD effectively assesses our primary concern for harm related to the intervention, namely, an adverse delay to intubation leading to reduced survival. The drawback of VFD is a potential dilution of harm (death) due to high efficacy (intubation rate) which is why we are also including days alive within 28 and 180 days as secondary outcomes. The 180 days mortality outcome will not be reported in the primary manuscript because we do not wish to delay dissemination of findings, but we consider it necessary to evaluate since many patients with COVID-19 have prolonged hospital stay. SpO2/FiO2 ratio is included as a sort of proof of concept outcome with the purpose of confirming or rejecting our underlying assumption that the higher PEEP enabled by the Helmet CPAP will improve lung aeration. We also have a patient-centred outcome regarding self-reported comfort. Both devices are reported to have superior tolerance compared to low-flow oxygen therapy and CPAP masks but they have never been tested head-to-head in adults. Device comfort may be particularly important if the trial does not show superiority or if the effect size is small. Lastly, we have included a secondary outcome on carbon dioxide rebreathing which, according to our judgement, is the main harm apart from death and comfort/tolerance issues that can be considered more likely for the intervention group than the control group. We are taking measure to avoid this from happening (i.e. minimum Helmet CPAP air flow 40 L/min).

### Participant timeline {13}

Please see Fig. 1 for the participant timeline.

**Fig. 1 Fig1:**
[figure not shown]
Participant timeline. Patients in the medical intermediate COVID-19 cohort ward will be screened for eligibility according to the inclusion and exclusion criteria, given written and oral information and then asked for written informed consent. Secondary endpoints will be collected at 1 h, 24 h and 28 days from randomisation, when the primary endpoint of ventilator-free days will also be assessed. We plan to include 60 patients in each group and expect the HFNC group to have ~ 19.5 VFD and the Helmet CPAP group to have ~ 23.3 VFD at 28 days. The thickness of the lines corresponds to the expected patient density in intervention versus control group and treatment in ward versus intensive care and in patients who survive or die within 28 days from randomisation. Abbreviations: SpO2, peripheral oxygen saturation; FiO2 ratio, fractional inspired oxygen concentration; RR, respiratory rate; PEEP, positive expiratory end-pressure; NEWS, national early warning score; AE, adverse events; VFD, ventilator-free days (within 28 days); ICU, intensive care unit; CPAP, continuous positive airway pressure

### Sample size {14}

We have estimated a required sample size of 120 patients (60 per group) to achieve 90% power to detect superiority at a 0.05 significance level. This estimate is based on the following clinical assumptions and statistical calculations:
A median of 1 out of 3 patients started on HFNC or Helmet CPAP will be started on invasive mechanical ventilation [2].Patients put on the ventilator will be treated in the ward for median 2.3 days before intubation, and ventilated patients will have 67.4% ICU mortality, and those who survive will stay on the ventilator for a median of 6 days [13].Patients not put on the ventilator will have 8.1% 28-day mortality and survive for a median of 7.5 days [2].The Helmet CPAP will avoid 3 out of 5 intubations compared to HFNC, which is an estimate based on (A) Frat et al. [4] who reported 40/106 (38%) intubation frequency in HFNC treated patients with AHRF versus 55/110 (50%) in patients with CPAP masks (*p* = 0.18 for comparison) and (B) Patel et al. [9] who reported 24/39 (61.5%) intubation frequency in patients with ARDS treated with CPAP mask versus 8/44 (18.2%) treated with Helmet CPAP (*p* < 0.001 for comparison). Hence, we expect treatment with Helmet CPAP to require (18.2/61.5)/(38/50) ≈ 2 out of 5 intubations compared to HFNC.

This leads to an estimated VFD of 19.545 for patients on HFNC (calculation: ((2/3*0.919*28) + (1/3*0.326*22))) and 23.257 for patients on Helmet CPAP (calculation: ((13/15*0.919*28) + (2/15*0.326*22))). We assume the standard deviation (SD) to be 6 in both groups based on a mean estimate of SDs reported from five trials with VFD as the primary endpoint in the paper by Yehya et al. [14]. Because we expect a reduction of intubation frequency and days in ventilator to be the driving factor behind a reduction in VFD rather than mortality, we will use Mann-Whitney *U* test as the primary statistical method, also based on argumentation by Yehya et al. [14]. In order to estimate the sample size, data was simulated with mean 23.257 for the intervention group and mean 19.545 for the control group, the standard deviation was set to 6 for both groups, and then the sample size was varied by simulation until the proportion of significant (0.05) two-sided Mann-Whitney *U* test was equal to the desired power (0.90) using R statistical software (See Additional file 1 for R code). This resulted in a required sample size of 60 patients per group.

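### The 90% power figure uses an SD of 6 that the protocol's own death and intubation rates rule out; on those rates, 60 per group gives about 57%

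*Protocol article*

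**What the plan says.** The abstract's Methods paragraph states: "We have estimated a required sample size of 120 patients randomised 1:1 to HFNC or Helmet CPAP to achieve 90% power". Sample size {14} gives the derivation.

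- **Means.** One in three HFNC patients is intubated, and the helmet leaves two intubations for every five on HFNC, so 2/15 are intubated. Mortality is 67.4% if ventilated and 8.1% if not. Ventilated survivors spend 6 days on the ventilator, so they score 22. The core of the HFNC calculation is "2/3*0.919*28) + (1/3*0.326*22"; the helmet line uses 13/15 and 2/15 instead. Deaths contribute nothing, in line with Outcomes {12}, which scores a death within 28 days as 0.
- **Spread.** The SD is taken as 6 in both groups, "based on a mean estimate of SDs reported from five trials with VFD as the primary endpoint".
- **Simulation.** "data was simulated with mean 23.257 for the intervention group and mean 19.545 for the control group", and "the standard deviation was set to 6 for both groups". The sample size was varied until 90% of two-sided Mann-Whitney tests were significant at 0.05. "This resulted in a required sample size of 60 patients per group".

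**The concern.** The means come from a fully specified three-point outcome. Once its probabilities are fixed, so is its SD, and there is no room to import a different one. With more than a quarter of control patients at 0 and most of the others at 28, the SD must be far above 6. The simulated data therefore describe a different, much tighter outcome than the one the protocol expects to observe, and the power claimed for the primary analysis belongs to that other outcome.

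What is at stake is how the result will be read. A trial believed to have 90% power would present a null finding as good evidence against a large benefit of the helmet. If the true power is not much better than even, that reading is wrong.

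**Working it through.** **1. Reproduce the stated figure.** The article does not name the simulated distribution, and the R code (Additional file 1) is not at hand. Normal data are the natural reading of a mean and an SD. With means 23.257 and 19.545, SD 6 and a two-sided Mann-Whitney test at 0.05, 20,000 simulations give power 0.900 at 59 and 0.906 at 60 per group. The stated 60 per group reproduces. Rounding the draws and clipping them to 0–28 leaves power at 0.902.

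**2. The distribution behind the means.** All inputs are from Sample size {14}.

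| | HFNC | Helmet CPAP |
|---|---|---|
| P(28) | 2/3 × 0.919 = 0.6127 | 13/15 × 0.919 = 0.7965 |
| P(22) | 1/3 × 0.326 = 0.1087 | 2/15 × 0.326 = 0.0435 |
| P(0) | remainder = 0.2787 | remainder = 0.1601 |
| Mean = 28·P(28) + 22·P(22) | 19.545 | 23.257 |
| E[X²] = 784·P(28) + 484·P(22) | 532.93 | 645.47 |
| Variance = E[X²] − mean² | 150.91 | 104.56 |
| SD | 12.28 | 10.23 |

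The means match the protocol exactly. The zero mass gives 60 × 0.2787 + 60 × 0.1601 = 26.3 deaths, which agrees with the roughly 26 events that Methods for additional analyses {20b} expects from the same rates.

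**3. Can an SD of 6 be rescued?** For a given mean m and probability of zero p, the SD is smallest when every survivor has the same value. It is then m × √(p/(1 − p)).

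- HFNC: 19.545 × √(0.2787/0.7213) = 12.15
- Helmet: 23.257 × √(0.1601/0.8399) = 10.15

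No choice of ventilator durations brings the SD near 6 while the stated means and death rates stand.

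**4. What the Mann-Whitney test sees.** The test responds to φ, the probability that a helmet patient has more ventilator-free days than an HFNC patient, with ties counted as half.

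- Normal data, SD 6: φ = Φ(3.712 / (6√2)) = Φ(0.437) = 0.669.
- Protocol's distribution: helmet higher = 0.7965 × (0.1087 + 0.2787) + 0.0435 × 0.2787 = 0.321; tied = 0.7965 × 0.6127 + 0.0435 × 0.1087 + 0.1601 × 0.2787 = 0.537. So φ = 0.321 + 0.537/2 = 0.589.

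The departure from 0.5 falls from 0.169 to 0.089, about half.

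**5. Power under the protocol's own distribution** (two-sided Mann-Whitney at 0.05, tie-corrected, by simulation):

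| Scenario | Power |
|---|---|
| 60 per group, as planned | 0.566–0.573 across runs |
| 60 per group, ventilator days spread around a median of 6 (lognormal, log-SD 0.3 or 0.8) | 0.57 |
| 120 per group | 0.85–0.86 |
| 135 per group | 0.89–0.90 |
| 140 per group | 0.90–0.91 |
| 60 per group, helmet avoids 85% of intubations | about 0.90 |

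**6. Sensitivity at 60 per group, 60% of intubations avoided.** Apart from the 38%, which {14} quotes from a cited trial, the alternative values are illustrative assumptions.

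| Change to one input | Power |
|---|---|
| Ventilated mortality 30–50% instead of 67.4% | 0.53–0.55 |
| HFNC intubation 38% instead of 1/3 | about 0.65 |
| HFNC intubation 50% | about 0.83–0.84 |
| Non-ventilated mortality 4% instead of 8.1% | about 0.65 |
| Non-ventilated mortality 0% | about 0.74–0.75 |

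None reaches 0.90.

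**The case against.** The strongest defence is that the arithmetic, taken on its own terms, is right. The SD of 6 is disclosed and has a cited source, and with the stated means it does give 60 per group. That stands: the fault is an assumption that conflicts with the protocol's other assumptions, not a slip in calculation. It does not rescue the figure, because a borrowed SD cannot override the variance that the trial's own rates already fix.

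A second point is that the distribution used in the simulation is inferred. This also stands, and with it the observation that normal draws would put about 21% of helmet values and 8% of HFNC values above the maximum of 28 matters little: clipping hardly changes the power. The loss comes from the missing mass at zero and the heavy ties. The lower bound on the SD in step 3 needs no assumption of normality.

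Third, 57% is sensitive to inputs. It rises to roughly 65–84% with more frequent intubation in the control group, or to 65–75% with fewer deaths outside the ventilator. It is therefore a base case and should be reported with a range.

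Finally, the Discussion concedes a modest sample size that may miss small but clinically important differences. On the protocol's inputs, however, the trial has a chance of about 43% (100 − 57) of missing the large effect it was planned for, and the concession does not cover that.

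**Conclusion.** The concern holds. The SD of 6 is incompatible with the death and intubation rates from which the same section derives its means; those rates imply SDs of 12.3 and 10.2. Under them, the planned test with 60 per group has about 57% power, not 90%. A power of 90% would need about 135 to 140 per group, or about 85% of intubations avoided with 120 patients. These figures rest on the protocol's planning rates taken at face value, with ventilated survivors scored at 22 days; spreading that value changes nothing material. Every alternative input tried at the planned effect left power below 90%. Because this is the headline design claim for the primary outcome and appears in both the abstract and {14}, it must be corrected.

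**What to change.** Rerun the Additional file 1 simulation by drawing each patient from the stated rates: intubated or not, dead or alive, and days on the ventilator if alive. Apply the tie-corrected two-sided Mann-Whitney test. In the abstract and in Sample size {14}, replace the 90% claim with the result (about 57% for 60 per group as base case, with a range over the intubation and mortality inputs). State the effect that 120 patients detect with 90% power (about 85% of intubations avoided). Extend the limitation in the Discussion so that it covers the planned effect as well as small ones.

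Enlarging the trial to about 135–140 per group is the alternative. The article reports that recruitment has begun, that incidence is low to moderate and that further centres were not feasible, so keeping 120 is defensible provided the power is stated correctly. The cost is a few lines of R, some reworded sentences and a less favourable power statement.
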